##### Physical function tests

Recommended OARSI physical function tests for clinical trials on people with hip osteoarthritis [69] will be used, including the 40-m fast-paced walk test, stair-climb test and the chair-stand test. All three tests have acceptable reliability with small measurement error in people with hip osteoarthritis [77], facilitating the ability to measure changes over time.

##### Self-reported physical activity

The International Physical Activity Questionnaire – short form is a self-administered questionnaire that aims to assess health-related physical activity [78]. Participants are asked to recall their physical activity over the last 7 days with regard to vigorous physical activity, moderate physical activity, walking and sitting.

##### Isometric hip-muscle strength

Isometric hip strength will be assessed using handheld dynamometer [79, 80]. Measurement of hip strength using hand-held dynamometry is reliable (ICC_2,1_ = 0.76–0.95) [79, 81]. Hip abduction, adduction, flexion, extension, internal rotation and external rotation will be measured bilaterally (Table 1). The peak force (N) produced from two trials separated by 15 s will be recorded for each action. Participants will be instructed to slowly build up their isometric strength against resistance until they reach their maximum, then maintain this level for 3 s, and slowly relax. Consistent encouragement will be provided via standardised audio recordings. The order of the action tested (e.g. flexion) will be randomly assigned between participants using marked cards that are selected out of a hat, and will remain consistent from pre-test to post-test. Torque (Nm) will be determined (*T* = Force (N) x moment arm (m)) and normalised to body mass (Kg) with the final unit of measurement being Nm/Kg.

**Table 1 Tab1:** Hip-muscle strength testing protocol

Action	Participant position	Dynamometer placement	Moment arm
Abduction	Supine. Participant holds onto the side of the plinth to stabilise	5 cm proximal to the lateral malleolus	Greater trochanter to 5 cm proximal to lateral malleolus
Adduction	Supine. Contralateral hip and knee flexed, with foot placed flat on the plinth. Participant holds onto the side of the plinth to stabilise	5 cm proximal to the medial malleolus	Greater trochanter to 5 cm proximal to medial malleolus, measured along the lateral surface of the lower limb.
Internal rotation	Sitting over the edge of the plinth. Arms folded across chest	5 cm proximal to the lateral malleolus	Lateral knee joint line to 5 cm proximal lateral malleolus
External rotation	Sitting over the edge of the plinth. Arms folded across chest	5 cm proximal to the medial malleolus	Medial knee joint line to 5 cm proximal medial malleolus, measured along the lateral surface of the lower limb
Hip flexion	Sitting over the edge of the plinth. Arms folded across chest	5 cm proximal to the proximal border of the patella	Greater trochanter to 5 cm proximal to proximal border of patella, measured along the lateral surface of the lower limb
Hip extension	Prone. Testing knee flexed to 90°	Calcaneus	Greater trochanter to Lateral joint line

Note: Resistance applied by the research assistant, with the exception of flexion and extension, where resistance is applied by a belt securing the dynamometer to an external anchor

##### Pain

The average pain over the previous week will be assessed using an 11-point numerical rating scale (NRS), anchored by 0 = ‘no pain’ and 10 = ‘worst pain possible’. The minimal important clinical difference is 1.8 [82].

##### Global hip questionnaires

Hip disability and Osteoarthritis Outcome Score (HOOS) [83, 84]: the HOOS consists of five subscales including (1) pain, (2) symptoms and stiffness, (3) activities of daily living, (4) sport and recreation and (5) quality of life. Participants respond to a 5-point Likert scale for each subscale, and the scores are converted to a 101-point scale, with 100 indicating the best possible score (no difficulty), and 0 indicating extreme symptoms. The HOOS questionnaire is considered reliable (ICC_2,1_ ranging from 0.75 to 0.97) [84].

##### Pain thoughts and depressive symptoms

Pain Catastrophizing Scale (PCS) [85]: the 13-item PCS aims to assess the participants’ thoughts and feelings associated with their pain. Using a 5-point Likert scale, participants are asked to rate the degree to which they have thoughts or feelings related to each item (e.g. ‘I worry all the time about whether the pain will end’). The scale is scored from 0 to 52 with higher scores indicating greater pain catastrophizing, and is associated with higher-intensity physical and emotional stress in response to pain [85]. The PCS is considered a reliable and valid measure of pain catastrophizing [85].

Brief Fear of Movement Scale for osteoarthritis (BFOM) [86]: adapted from the Tampa Scale of Kinesiophobia [87], the BFOM aims to assess the degree to which participants with osteoarthritis feel that physical movement will cause pain, injury or re-injury [86]. The six-item scale is scored from 0 to 24, with a higher score indicating lower fear of movement (better score).

Patient Health Questionnaaire-9 (PHQ-9) [88]: the PHQ-9 is a nine-item valid and reliable scale that aims to measure depression severity. Scored from 0 to 27, participants can be classified as having mild (≥ 5), moderate (≥ 10), moderately severe (≥ 15) and severe (≥ 20) depressive symptoms.

##### Quality of life

Assessment of Quality of Life Questionnaire (AQoL-8D) [89, 90]: the AQoL-8D contains 35 items that assess dimensions of quality of life related to independent living, happiness, mental health, coping, relationships, self-worth, pain and senses. It is a reliable and valid tool [90] that can produce a weighted utility score (0–1), or an unweighted, health-related quality of life score (0–100) with higher scores representing better quality of life.

##### Global change

Global Rating of Change (GROC) [91]: the GROC consists of an 11-point Likert scale that asks participants to rate their perceived overall change in condition of their hip from the beginning of the study. A version of the GROC used in a previous study on hip pain [92] has been adapted for use in this study. A score of ‘0’ will equate to ‘no change’. If ‘better/worse’, participants will be asked to rate the degree of change from ‘slightly better/worse’ to ‘very much better/worse’, with scores ranging from + 1 to + 5 for ‘better’ and − 1 to − 5 for ‘worse’. Scores will further be dichotomised to define ‘success’ as those with a score of ‘moderately better’ to ‘very much better’ (i.e. + 3 or more).

##### Gluteal-muscle activity

Muscle function of the gluteal muscles will be assessed with an EMG in a subset of 30 participants. Fine-wire electrodes will be inserted into GMed and GMin using previously validated procedures [93, 94]. Muscle activity will be recorded during six walking trials across a 10-m pathway. Amplitude and timing variables will be determined during the stance phase of the gait cycle as reported previously [33, 95].

##### Gluteal-muscle size and adiposity

Muscle volume and adiposity will be assessed with MRI in a subset of 30 participants (the same participants undergoing EMG testing). Muscles of interest will include GMin, GMed and gluteus maximus, as well as tensor fascia lata. Muscle volume and adiposity will be determined through off-line processing of de-identified images using customised MATLAB software (The MathWorks, Inc., Natick, MA, USA) [96]. Axial slices of each muscle will be traced to establish cross-sectional area, and multiplied by slice thickness to calculate volume [26, 97]. To determine muscle adiposity, a Muscle-Fat Index (MFI) will be calculated from the axial slices as the proportion of adipose tissue to total muscle (fat/fat + muscle) [98]. This technique has been validated against the ‘gold standard’, biopsy [99]. Given the segmental nature of GMin and GMed, a MFI will be calculated for anterior and posterior regions of each muscle [96].

### Trial follow-up

The primary time-point will be at the completion of the intervention (13 weeks). Additional measures of some outcomes (questionnaires) will be recorded at 7 and 25 weeks. The schedule of enrolment, assessment, intervention and follow-up can be seen in Fig. 2.

**Fig. 2 Fig2:**
[figure not shown]
Standard Protocol Items: Recommendations for Interventional Trials (SPIRIT) Checklist: patient schedule of procedures

### Success of blinding

The success of participant blinding will be assessed 1 week after commencing the intervention by having participants nominate which intervention they feel they have been allocated to (‘generalised exercise programme’ or ‘targeted gluteal programme’ or ‘unsure’. It is not anticipated that large differences in outcome would be present 1 week after commencing the intervention, so the potential benefit (or otherwise) of the intervention will not influence their decision. The validity of assessing the effectiveness of blinding for interventions that may expect large effect sizes is questionable, and is now no longer a mandatory component of the Consolidated Standards of Reporting Trials (CONSORT) Statement [100, 101].

### Adverse events

Adverse events will be monitored and recorded by the physiotherapist and participant. These may include minor aches and pains through to serious adverse events (e.g. myocardial infarction) associated with beginning a new exercise programme.

### Sample size and power analysis

The minimal clinically important difference for the WOMAC is 6 physical function units [72]. Using data from the sham intervention of a previous RCT in people with hip osteoarthritis [21], the standard deviation (SD) of change in the WOMAC over 13 weeks is 9.2 units, assuming a baseline to follow-up correlation of 0.60. A total sample size of 76 participants (38 per group) is required to detect a clinically important difference between sham and intervention groups, with a power of 80% and an alpha of 0.05. A clinically important difference of 6 units between groups, assuming a within-group SD of 9.2 units equates to a moderate to large effect size (0.65). To account for potential drop-outs similar to those reported in previous studies [21] we will recruit 90 participants (45 per group).

### Statistical analysis

Statistical analysis will be using intention-to-treat principles and on a per-protocol basis. Data analysed will focus on detecting the between-group treatment and within-group treatment effects (with effect sizes and 95% confidence intervals) at each of the follow-up time-points. A linear mixed model will be used for the primary analysis of the changes in the WOMAC due to its advantages in modelling the influence of nonlinear, individual differences over time. Adjustments will be made for the respective baseline outcome measures, as well as age, sex and BMI; and adjustments for other baseline variables that have evidence of imbalances between groups (e.g. radiographic severity). The secondary outcomes will be assessed using *t* tests or Mann-Whitney *U* tests, adjusting for baseline differences if required. The Global Rating of Change Scale will be dichotomised to define ‘success’ as those with a score of ‘moderately better’ to ‘very much better’ (i.e. + 3 or more). A generalised mixed model (adjusted for baseline differences and covariates) will be used to assess differences in the proportion of ‘successes’ between groups over each time-point.

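### Secondary outcomes are assigned tests that cannot perform the baseline adjustment the plan mentions, and adjusting only if required gives up precision

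*Protocol article*

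**What the plan says.** All of this is in the protocol article, mostly in one paragraph of the Statistical analysis section.

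- Primary outcome: "A linear mixed model will be used for the primary analysis of the changes in the WOMAC". The covariates follow without any condition: "Adjustments will be made for the respective baseline outcome measures, as well as age, sex and BMI".
- Secondary outcomes: "The secondary outcomes will be assessed using *t* tests or Mann-Whitney *U* tests, adjusting for baseline differences if required". The text does not say what makes adjustment required, which method then replaces the two tests, or whether follow-up or change scores are compared.
- One secondary outcome is treated separately. For success on the dichotomised Global Rating of Change (GROC), "A generalised mixed model (adjusted for baseline differences and covariates) will be used to assess differences in the proportion of" successes between groups.
- Treatment effects are to be reported "with effect sizes and 95% confidence intervals".

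The only planning correlation is in Sample size and power analysis, for the WOMAC: "assuming a baseline to follow-up correlation of 0.60". No correlation is given for any secondary outcome.

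**The concern.** A two-sample t test and a Mann-Whitney test each compare two groups on one variable. Neither has a term for a baseline value, so once adjustment is judged necessary, the analyst must move to a method the plan does not name. Because the trigger is not defined either, two statisticians following this sentence could analyse the same outcome differently, depending on the imbalance they saw and how they judged it.

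The default branch also makes less use of data the trial collects. Accelerometry, function tests, strength, pain, HOOS, the psychological scales, quality of life, EMG and MRI can all have a pre-treatment value. Leaving that value out, or using it only by subtraction, gives wider confidence intervals than the same data allow. This matters most for EMG and MRI, which are limited to 30 participants and which the Discussion relies on for mechanistic evidence of a difference or of its absence.

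**Working it through.** **1. The plan's own figure.** Inputs from Sample size and power analysis: difference 6 units; "the standard deviation (SD) of change in the WOMAC over 13 weeks is 9.2 units"; power 80%; alpha 0.05, taken as two-sided. Normal approximation, per arm: 2 × (1.96 + 0.8416)² × (9.2/6)² = 2 × 7.849 × 2.351 = 36.9, so 37. The exact t-test calculation gives 37.9, so 38 per arm and 76 in total, with power 80.1%. The stated 76 reproduces. It concerns the WOMAC and does not depend on this point.

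**2. Variance of three analyses.** Let σ² be the variance at one time-point (assumed equal at baseline and follow-up) and ρ the correlation between them. The variance per observation is:

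- t test on follow-up scores: σ²
- t test on change scores: 2(1 − ρ)σ²
- ANCOVA with the baseline value: (1 − ρ²)σ²

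Relative to ANCOVA, the follow-up test therefore has 1/(1 − ρ²) times the variance, and the change-score test 2(1 − ρ)/(1 − ρ²) = 2/(1 + ρ) times.

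| Assumed ρ | Follow-up t test vs ANCOVA | Change-score t test vs ANCOVA |
|---|---|---|
| 0.3 | 1/0.91 = 1.10 | 2/1.3 = 1.54 |
| 0.6 | 1/0.64 = 1.56 | 2/1.6 = 1.25 |
| 0.8 | 1/0.36 = 2.78 | 2/1.8 = 1.11 |

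The 0.6 row uses the protocol's WOMAC correlation; for every secondary outcome all three rows are assumptions. At 0.6, confidence intervals are √1.5625 = 1.25 times as wide on follow-up scores and √1.25 = 1.12 times as wide on change scores. These ratios ignore the small cost of estimating one slope.

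**3. What that means for power.** The plan gives no target difference for secondary outcomes, so assume a difference of 0.5σ and ρ = 0.6. Residual SDs are then σ, √0.8 σ = 0.894σ and √0.64 σ = 0.8σ. Power = Φ(0.5σ/SD × √(n/2) − 1.96), with n per arm:

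| n per arm | Follow-up | Change | ANCOVA |
|---|---|---|---|
| 38 (evaluable target) | 59% | 68% | 78% |
| 15 (EMG and MRI, 30 at 1:1) | 28% | 33% | 40% |

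**4. Does conditional adjustment raise the false-positive rate?** This was simulated with no treatment effect, 38 per arm and 40,000 trials per setting. The assumed rule was a t test on follow-up scores unless baseline differed at p < 0.05, and ANCOVA otherwise. Type I error at nominal 0.05 was 0.046, 0.038 and 0.030 for ρ = 0.3, 0.6 and 0.8. ANCOVA applied every time gave 0.050, 0.048 and 0.051. The conditional rule was conservative, not inflated.

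**The case against.** The strongest reply is that the sentence can be read as two steps: t or Mann-Whitney by default, and an adjusted model where needed, with that model left to the full protocol or analysis plan. Part of this stands. The unadjusted tests run as written, so a reader who infers that the secondary analysis cannot be carried out goes too far; only the adjusted branch lacks a method. But the article does more than omit detail. It fixes two tests and makes adjustment conditional, and that is the choice that loses precision.

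It can also be said that the plan never states that follow-up scores are tested. The sample size and the primary analysis both speak of change, and a change-score test does use the baseline. This is fair, and the 1.56 figure should not be quoted alone. The change-score ratio still exceeds 1 throughout the range.

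The adjustment sentence for the primary analysis might be read as covering all outcomes, since it refers to baseline outcome measures in the plural. On that reading the condition in the next sentence contradicts it, so the text still needs correcting.

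Four stronger inferences are tempting but unsupported:

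- **More false positives.** The check above found the opposite under a fixed trigger, and the documents describe no selective choice after results are seen.
- **Mann-Whitney conflicts with the promised confidence intervals.** The plan promises effect sizes, not mean differences, and a Hodges-Lehmann shift with its interval would meet that.
- **The tests breach intention to treat by dropping missing visits.** Missing-data handling may be set elsewhere, and ANCOVA on a single follow-up drops the same participants unless values are imputed.
- **Power computed from the WOMAC difference and SD applies to secondary outcomes.** Those planning values belong to the primary outcome, which is not analysed by t test.

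**Conclusion.** The point holds for continuous secondary outcomes with a baseline value. The named tests cannot perform the adjustment mentioned, its trigger is undefined, and the default analysis is less precise than one that always includes baseline.

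The size depends on correlations the protocol does not give for these outcomes. At 0.60 the variance excess is 56% on follow-up scores or 25% on change scores. Over 0.3 to 0.8 it runs from 10% to 178% on follow-up scores and from 54% down to 11% on change scores. These figures assume equal variances at the two time-points.

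The consequence is lost precision and an open analysis choice in secondary outcomes. The primary WOMAC analysis, the sample size of 76 (90 recruited) and the dichotomised GROC analysis are not affected.

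**What to change.** Replace the sentence on secondary outcomes, deleting the words *if required*, and specify:

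1. Every continuous secondary outcome with a baseline value is analysed with that value always included, whatever imbalance is observed.
2. Questionnaires repeated at 7, 13 and 25 weeks use a baseline-adjusted linear mixed model, as for the WOMAC. Outcomes with one follow-up use ANCOVA.
3. Site, the randomisation stratum, is included for multi-site outcomes. It is left out for EMG and MRI, which are collected at Bendigo only, so site is constant. With about 15 per arm there, baseline alone is enough.
4. Skewed outcomes use a transformation, a bootstrap confidence interval or rank-based ANCOVA, with the choice stated in advance.
5. GROC is excluded because it has no baseline value. Its dichotomised form keeps the generalised mixed model already stated.

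The cost is a change of wording and slightly more analysis work. No new data, visits or participants are needed.

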## Discussion

This RCT will be the first to investigate the effect of a targeted gluteal rehabilitation programme compared to a sham exercise programme for improving physical function in people with hip osteoarthritis. The targeted GHOst protocol is a structured exercise programme that incorporates gait retraining, motor control and high-intensity resistance exercises. It requires minimal equipment and is implemented by community physiotherapists. This pragmatic design could enable easy integration into any physiotherapy clinical setting. The research design aims to minimise bias associated with selection, measurement and confounding. The results of this study will have significant implications in terms of maximising physical function in people with hip osteoarthritis which may ultimately affect their quality of life.

The GHOst intervention has been specifically developed for people with hip osteoarthritis. Selection of a sample of people with hip osteoarthritis is, therefore, critical to the outcome of this study. We have used an accepted criteria for hip osteoarthritis diagnosis that includes clinical and radiographic confirmation [44]. More recent criteria, for example from the National Institute for Health and Care Excellence (NICE) [13], suggests a clinical diagnosis without the need for radiographic confirmation. Such criteria would enhance generalisability and potentially maximise recruitment rates into the study. However, clinical diagnoses without radiographic confirmation are often paired with higher age thresholds (NICE guidelines; > 45 years) to improve the specificity of the diagnosis. It is increasingly being recognised that osteoarthritis is not just an ‘old-persons’’ disease [102]. A large increase in prevalence of osteoarthritis has been observed in Canadians aged over 35 years (1994–2002 data) [103], and the projected change in healthcare costs associated with osteoarthritis in Australia in those under 65 years is greatest in the 35–44 years age bracket [7]. Radiographic confirmation would, therefore, allow for inclusion of younger people with osteoarthritis, who may have a significant impact on the burden of disease in years to come.

Measurement error and confounding have been limited through the study design. All assessors are blinded to group allocation, and our primary outcomes are valid and reliable. A unique element of the current study is the inclusion of secondary outcomes such as muscle activity (EMG) and muscle size (MRI), which will provide mechanistic evidence of differences (or lack of) between interventions. It is not possible to blind the therapists to group allocation, and this may confound the effects of the intervention if therapists deliver the GHOst intervention with more enthusiasm than the sham. This could potentially lead to inflated effect sizes in favour of the intervention. This will be minimised with appropriate training for therapists on delivery of both interventions with equal enthusiasm.

The results of this study will be disseminated via journal publication and conference presentations. Participants will receive a summary of results via email at the completion of the study. The interventions have been designed to facilitate translation into clinical practice and will aid health and medical practitioners with evidence-based decision-making for the non-pharmacological management of hip osteoarthritis.

## Trial status

This is protocol version 3 (20 October 2017). Recruitment commenced 26 July 2017. Recruitment is expected to be completed by 1 June 2019.

## Abbreviations

ANZCTR: Australian and New Zealand Clinical Trials Registry
AQoL-8D: Assessment of Quality of Life Questionnaire-8D
BFOM: Brief Fear of Movement Scale for Osteoarthritis
BMI: Body Mass Index
CONSORT: Consolidated Standards of Reporting Trials
EMG: Electromyography
FABER: Flexion, abduction, external rotation test
GHOst: Gluteal exercises for Hip Osteoarthritis
GMed: Gluteus medius
GMin: Gluteus minimus
GROC: Global Rating of Change
HDEC: Health and Disability Ethics Committee
HOOS: Hip Osteoarthritis Outcome Score
HREC: Human Research Ethics Committee
MFI: Muscle-Fat Index
MRI: Magnetic resonance imaging
MVPA: Moderate to vigorous physical activity
NICE: National Institute for Health and Care Excellence
NRS: Numerical rating scale
NSAIDS: Non-steroidal anti-inflammatory drugs
PCS: Pain Catastrophizing Scale
PHQ-9: Patient Health Questionnaire-9
SD: Standard deviation
SPIRIT: Standard Protocol Items: Recommendations for Interventional Trials
UTN: Universal Trial Number
VAS: Visual analogue scale
WOMAC: Western Ontario and McMaster Universities Osteoarthritis Index
